In sum, there is an urgent need to improve the quality of children’s dietary intake. Optimizing school meals within the NSLP can have a significant public health impact. Tremendous resources have been invested in school salad bars as a means to increase FV intake, yet it is not known if they achieve this goal. By randomly selecting schools receiving salad bars, matching them with those serving pre-portioned FV only, and conducting a comprehensive, longitudinal evaluation that includes objective, validated assessments of dietary intake, this investigation will address these critical gaps. Specifically, this study will identify: (1) how salad bars impact dietary consumption in NSLP lunches, and (2) consequences of, and barriers and facilitators associated with, salad bar implementation. It will also examine the potential moderating role of the school-level sociodemographic factors of percent high obesity risk racial/ethnic minority students and Title I status on dietary consumption, and salad bar implementation barriers and facilitators. In the current study, all FVs on the salad bars will be fresh and *replace* all fixed portion FVs on the serving line. All schools will operate under a policy requiring students to take at least one FV serving [44]. This will allow examination of the independent and combined impact of variety and choice, two mechanisms with potential to increase FV intake, within the NSLP. We hypothesize that schools with salad bars will manifest greater increases in both FV selection and consumption, and decreases in FV waste, compared with schools without salad bars. In addition, we hypothesize that schools with salad bars will have greater improvements in dietary quality and reductions in total energy intake at lunch, compared with schools without salad bars.

Data from this trial will yield some of the clearest evidence related to salad bars to date, providing a strong evidence base to evaluate school nutrition policies designed to enhance dietary intake and reduce health disparities within the NSLP. Results can guide resource allocation and inform targeted interventions and policies designed to reduce obesity.

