### Design

Twelve pairs of matched schools will be randomly selected: half will receive a salad bar (Intervention; replacing all other FVs) and half will only serve pre-portioned FVs, standard under the NSLP (Control). Thus, groups will have different FV presentation methods; however all schools will be operating under a policy requiring students to take at least one FV serving [44]. In contrast to prior salad bar research, [28] salad bars in the current study will replace all other FVs on the lunch line, and students can select their entire meal from the salad bar. This implementation model facilitates a more rigorous comparison between schools with and without salad bars than that conducted in prior research. Schools will be matched on Title I status (a proxy for socioeconomic status [SES]) and percent of racial/ethnic minority students based on higher obesity risk. Dietary intake at lunch will be objectively assessed in each pair of schools, prior to (baseline), and 4–6 weeks after salad bars are installed (post), resulting in ~ 14,160 lunch observations throughout the study duration. The primary dependent variable of interest is change in FV intake, assessed using digital imagery plate waste methods. Cafeteria sales and NSLP participation data will also be examined to assess the potential impact of salad bars on these critical revenue sources. Finally, we will assess implementation practices and cafeteria personnel’s perspectives, to identify barriers and facilitators to salad bars and inform sustainability efforts.

Prior to random selection, each school will be assigned to one of 4 categories based on sociodemographic variables. We used information from schools that received salad bars in the first 2 years of the district’s program (prior to the current study) to develop matching procedures. Matching was based on: 1) Title I status, which includes % free and reduced-price lunch, and 2) % of students from racial/ethnic backgrounds at higher risk of obesity (Native American, African American/Black, Latinx, Native Hawaiian/Pacific Islander, more than one race). Four categories of schools resulted: A = < 40% minoritized AND not Title I; B = 40–60% minoritized AND not Title I; C = 40–60% minoritized AND Title I; and D = > 60% minoritized AND Title I. Matching procedures were then applied to the remaining 91 schools, demonstrating that each category has adequate numbers of schools in each year of this study to successfully execute the proposed aims.

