As illustrated in Fig. 1 and 16 different schools will be included (A1➔D4), 4 from each sociodemographic category. In Year 1, 8 schools will be randomly selected: 4 with salad bars (A1➔D1; Intervention), matched with 4 serving pre-portioned FVs only (A2➔D2; Control). In Year 2, these 4 control schools will receive salad bars and become Intervention schools, and will be matched with 4 new, randomly selected Control schools (A3➔D3). These procedures will be repeated in Year 3, with A3➔D3 becoming Intervention schools, matched with new randomly selected Control schools (A4➔D4). There will ultimately be 12 pairs of matched schools (12 Intervention [shaded green in Fig. 1] and 12 Control [shaded yellow]).

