## Statistical analyses

### Power analysis

Power and effect size of the multilevel models that will be used to analyze the variety of outcomes in our cluster RCT are a function of a number of parameters: (1) the number of clusters (J = 16 independent schools [8 Intervention and 8 Control]), (2) the cluster size (*n* = 295 lunches per school), and (3) the ICC (estimated as 0.01, 0.05, and a much more conservative 0.10), which takes into account the correlated nature of our data and is the ratio of variability between clusters to the total variability [66]. Optimal Design Plus Empirical Evidence v3.01 software [67] was used to calculate the minimum detectable effect size given the parameters above, α = 0.05, and a desired power of 80%. For ICCs of 0.01, 0.05, and 0.10, we have 80% power to detect small to medium effect sizes of 0.17, 0.35, and 0.48, respectively. Thus, our proposed sample of 14,160 observations will be more than adequate to evaluate the study aims.

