### Analyses

Prior to analyses, distributions of all measures will be examined. Contingency tables and frequency distributions will be evaluated (for categorical and continuous variables, respectively), and transformations considered. Outliers will be checked for errors before being used in analyses. Sex differences will be assessed for all outcomes; if significant differences are found, analyses outlined below will be stratified by sex. All tests will be 2-sided at α = 0.05 level, corrected for multiple comparisons, and conducted in SAS v9.3.

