We will evaluate differences in dietary quality (assessed with the HEI) [57] for the total lunch and energy intake (kcals) for the total lunch, FVs, non-FVs, and beverages between Intervention and Control schools. MLM will be applied to examine the association between levels of FV intake and overall calorie consumption at lunch, both independent of school group as well as between Intervention and Control schools, to inform obesity prevention efforts.

Monthly sales (and reimbursements) and NSLP participation data will be characterized using descriptive statistics and graphical approaches. Changes in FV sales (and reimbursements) per student (based on enrollment) and % NSLP participation will be calculated (based on the total number of days lunch was served), evaluated by month. Schools will be compared on these outcomes using paired t-tests (matching on month for each school pair). Responses from cafeteria surveys and process logs will be examined to identify barriers and facilitators and implementation differences related to salad bars to inform sustainability. These variables will also be considered as potential factors explaining any differential findings between schools. Open-ended survey responses will be qualitatively examined for common themes by two independent raters, guided by thematic analysis, to identify, analyze and report themes within and across data [68]. This realistic method allows for meaning to come from participants, rather than from pre-existing codes [69].

To examine the potential differential responses to salad bars among sociodemographic groups, main effects for Title I status and race/ethnicity school group (A through D) will be examined in Aims 1 through 3 analyses. If main effects are observed, models will be stratified by sociodemographic group and moderator analyses considered as appropriate.

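### The power calculation supports only the average effect over 16 schools, yet the adequacy claim covers all study aims, including moderation, where power by the same formula is about 15-43%

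*Protocol article*

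**What the plan says.** The Power analysis section bases its calculation on "the number of clusters (J = 16 independent schools [8 Intervention and 8 Control"], with 295 lunches per school, ICC values of 0.01, 0.05 and 0.10, and "α = 0.05, and a desired power of 80"%. It reports detectable effects of 0.17, 0.35 and 0.48 and concludes: "Thus, our proposed sample of 14,160 observations will be more than adequate to evaluate the study aims".

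The Background gives a further purpose: "It will also examine the potential moderating role of the school-level sociodemographic factors of percent high obesity risk racial/ethnic minority students and Title I status". The Design section adds that the matching was developed so that moderation by race/ethnicity and SES could be evaluated. It also fixes the numbers: "16 different schools will be included (A1➔D4), 4 from each sociodemographic category". These form 12 matched pairs over three years, so 3 pairs per category. Categories A and B are not Title I; C and D are.

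The Analyses section examines main effects of Title I status and of category A-D in the analyses of Aims 1 to 3, and continues: "If main effects are observed, models will be stratified by sociodemographic group and moderator analyses considered as appropriate". The article gives no detectable effect for a stratum, a category or an interaction.

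**The concern.** The calculation concerns one contrast that uses all 16 schools. A difference in effect by Title I status compares two halves of the schools, and a model for one category has 4 schools. Both moderators are properties of the school, so the number of schools largely sets the precision. The total of 14,160 lunches is therefore the wrong quantity to cite as reassurance for these analyses.

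The Discussion says that examining moderation will lead to targeted efforts for the children at greatest risk of obesity. A non-significant Title I contrast, or a null result in category D, would be read next to a published statement that the sample is more than adequate. The reader could take it as evidence of no difference, or of no effect, when the design had little chance of showing one.

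**Working it through.** **Inputs.** J = 16 schools (8 v 8), n = 295, ICC ρ = 0.01, 0.05, 0.10, two-sided α = 0.05, power 80% (Power analysis); 4 schools and 3 pairs per category, 12 pairs in all, 8 schools at each Title I level (Design).

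**Formula.** Variance of a school mean in SD units: v = ρ + (1 − ρ)/295, which is 0.01336, 0.05322 and 0.10305. Power comes from the noncentral F distribution with 1 and df degrees of freedom and noncentrality (d/SE)².

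**Step 1: reproduce the plan.** SE = √(4v/16) = 0.0578, 0.1153, 0.1605, with df = 14. The effects detectable with 80% power are 0.174, 0.348 and 0.484, which match the stated 0.17, 0.35 and 0.48.

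**Step 2: same formula, same effects, other contrasts.** The detectable effect scales with √v, so at the unrounded effects each power is the same for all three ICCs. With the rounded stated effects the results move by at most about 2 percentage points.

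| Contrast | SE | SE at ICC 0.05 | df | Power | Detectable at 80%, ICC 0.05 |
|---|---|---|---|---|---|
| Average effect, 16 schools | √(v/4) | 0.115 | 14 | 80% | 0.35 |
| Title I difference in effect, 16 schools, 4 per cell | √v | 0.231 | 12 | 28% | 0.70 |
| Title I difference in effect, 6 v 6 pairs treated as independent | √(2v/3) | 0.188 | 10 | 39% | 0.59 |
| Effect within a Title I stratum, 8 schools | √(v/2) | 0.163 | 6 | 43% | 0.55 |
| Effect within one category, 2 v 2 schools | √v | 0.231 | 2 | 15% | 1.30 |
| Effect within one category, 3 pairs analysed as pairs | √(2v/3) | 0.188 | 2 | 20% | 1.07 |
| Effect within one category, 3 v 3 treated as independent | √(2v/3) | 0.188 | 4 | 30% | 0.71 |

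The two SEs for the Title I difference arise as follows. With 4 schools in each of four arm-by-Title I cells, the variance is 4 × v/4 = v. With 6 pairs at each level and a pair difference of variance 2v, it is 2 × 2v/6 = 2v/3.

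**Step 3: baseline adjustment.** The formula uses post-installation means only, while the primary variable is change in intake and baseline differences are to be controlled. The article gives no baseline correlation, so this step is an assumption range. If adjustment removes a share R of between-school variance, v becomes ρ(1 − R) + (1 − ρ)/295. Power at the same effects, across the three ICCs:

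| Contrast | R = 0 | R = 50% | R = 75% |
|---|---|---|---|
| Title I difference, 16 schools | 28% | 42-49% | 55-76% |
| Title I difference, 12 pairs | 39% | 56-64% | 71-89% |
| One category, 3 v 3 | 30% | 43-50% | 56-75% |

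**Step 4: multiplicity.** The Analyses section says: "All tests will be 2-sided at α = 0.05 level, corrected for multiple comparisons, and conducted in SAS v9.3". The tables use uncorrected α. A Bonferroni correction over four categories would lower the R = 0 category figures to about 4% (2 v 2) or 10% (3 v 3).

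**The case against.** The best defence is that no stated number is wrong, and that a trial is normally powered on its main contrast. The Background numbers two things the study will identify and adds moderation afterwards, with no hypothesis attached. The Analyses section makes stratification conditional and moderator analyses discretionary, which is close to exploratory status. All this is fair, and it makes the point one of unrestricted wording and not of faulty arithmetic. It does not remove it: the Background states moderation as something the study will examine, the Design section says the matching was built for it, and the Analyses section attaches it to Aims 1 to 3.

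Several stronger readings are tempting, and the article does not support them:

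- A reader might infer that the plan claims 80% power for moderation. It does not; it gives no figure for it.
- A reader might take the Design section's phrase "demonstrating that each category has adequate numbers of schools in each year of this study to successfully execute the proposed aims" as a second power claim. It reports the result of applying the matching to the remaining 91 schools, that is, whether each category holds enough schools to draw from. It needs no change.
- A reader might treat the low powers as best case because α is uncorrected. They are not an upper bound: the formula ignores baseline adjustment, and under the 75% assumption the 12-pair Title I contrast passes 80% at ICC 0.05 and 0.10.
- A reader might say that more lunches cannot help at all. At ICC 0.01 the lunch-level term, 0.99/295 = 0.00336, is 25% of v = 0.01336, so lunches matter there; at ICC 0.05 and 0.10 the share is 6% and 3%.
- A reader might infer that the plan intends to conclude no effect from a null stratum. No section says so; the risk lies in how such a result would be read.

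**Conclusion.** The concern holds for the adequacy sentence only. The detectable effects of 0.17, 0.35 and 0.48 are right for the average effect over 16 schools, and they do not carry over to moderation. By the same formula without baseline adjustment, power at those effects is about 28-39% for a Title I difference in effect, 43% within a Title I stratum, and 15-30% within one category. The 39% belongs to the contrast of 6 v 6 pairs, not to a single category.

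These figures rest on the article's ICCs, uncorrected α, the full three-year design, and no gain from baseline or matching. If baseline adjustment removed 50-75% of between-school variance, the Title I difference would have about 42-76% power (16 schools) or 56-89% (12 pairs), and one category (3 v 3) about 43-75%. Adequacy for moderation is therefore not shown by the calculation given, and it could be claimed for the Title I contrast only under favourable assumptions that the article does not state.

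**What to change.** 1. In the Power analysis section, limit the adequacy sentence to the average Intervention-Control effect over all schools.
2. Beside it, state the detectable difference in effect for moderation under the final model, including its baseline adjustment and its handling of schools that serve in both arms. Without adjustment the Title I figure is about 0.59-0.70 SD at ICC 0.05.
3. In the Analyses section, label moderation exploratory. Report arm-by-moderator contrasts with 95% confidence intervals from one pooled model in place of category-stratified models. Draw no conclusion of no effect or no differential effect from category models of 3 pairs.

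The cost is a few sentences and one short calculation, with no new schools or data. The downside is a less favourable stated capability for the moderation objective.

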### Analyses

Prior to analyses, distributions of all measures will be examined. Contingency tables and frequency distributions will be evaluated (for categorical and continuous variables, respectively), and transformations considered. Outliers will be checked for errors before being used in analyses. Sex differences will be assessed for all outcomes; if significant differences are found, analyses outlined below will be stratified by sex. All tests will be 2-sided at α = 0.05 level, corrected for multiple comparisons, and conducted in SAS v9.3.

Analyses are dictated by the cluster RCT study design. Data are hierarchical, gathered in multiple levels. The first level of measurement is from students, clustered within schools, the second level of measurement. We are measuring consumption based on students, yet their treatment assignment is defined by the school’s assignment. This nested structure must be considered in analyses as the assignment of intervention to the schools can result in students within schools being positively correlated for the outcomes. Without accounting for correlated nature of the data, Type 1 error rate for the intervention effect might be inflated and the significance of the study findings misinterpreted. Multilevel Linear Modeling (MLM) is a type of regression used to analyze nested data as it can accommodate fixed and random effects and correlated observations within units of assignment (schools). SAS PROC MIXED (for continuous variables) and PROC GLIMMIX (for dichotomous and polytomous data) have MLM applications which take into account random effects and correlated observations and will be used in these analyses. Potential covariates include grade, NSLP participation, and month of assessment, and factors related to the school cafeteria environment that might differ between schools (e.g., lunch duration), where appropriate. Using these models, we will evaluate differences between Intervention and Controls schools in types and variety of FVs and categories of vegetables selected, and subsequent consumption (% consumed/wasted) at baseline and 4–6 weeks after salad bars are installed. Variety will be recorded as the number of different types of FVs selected for each meal, and the number of categories of vegetables (ranging from 1 to 5; corresponding with USDA categorization) [44]. For the primary outcome (FV consumption), plate waste ratings will be calculated for fruits, vegetables, each specific FV category, and also averaged across FVs. We will also evaluate the effect of location of FVs (salad bar, lunch line, or at the point of sale) and serving type (self-serve, pre-portioned) of each item on FV selection and consumption to inform best implementation practices.

We will evaluate differences in dietary quality (assessed with the HEI) [57] for the total lunch and energy intake (kcals) for the total lunch, FVs, non-FVs, and beverages between Intervention and Control schools. MLM will be applied to examine the association between levels of FV intake and overall calorie consumption at lunch, both independent of school group as well as between Intervention and Control schools, to inform obesity prevention efforts.

Monthly sales (and reimbursements) and NSLP participation data will be characterized using descriptive statistics and graphical approaches. Changes in FV sales (and reimbursements) per student (based on enrollment) and % NSLP participation will be calculated (based on the total number of days lunch was served), evaluated by month. Schools will be compared on these outcomes using paired t-tests (matching on month for each school pair). Responses from cafeteria surveys and process logs will be examined to identify barriers and facilitators and implementation differences related to salad bars to inform sustainability. These variables will also be considered as potential factors explaining any differential findings between schools. Open-ended survey responses will be qualitatively examined for common themes by two independent raters, guided by thematic analysis, to identify, analyze and report themes within and across data [68]. This realistic method allows for meaning to come from participants, rather than from pre-existing codes [69].

To examine the potential differential responses to salad bars among sociodemographic groups, main effects for Title I status and race/ethnicity school group (A through D) will be examined in Aims 1 through 3 analyses. If main effects are observed, models will be stratified by sociodemographic group and moderator analyses considered as appropriate.

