**Fig. 1 Fig1:**
[figure not shown]
Design of wait-list control randomized controlled trial of school salad bars

Each pair of Intervention and Control schools will be assessed concurrently, minimizing the threats maturation and history effects pose to internal validity [45]. Baseline and post-assessments within each pair will be conducted on days with the same menu cycle whenever possible, which controls for potential confounds, such as the varying palatability of meals and seasonal variations in food availability (the district’s schools have 5 week menu cycles). We will also control for month of assessment in all analyses. This is particularly important in the elementary school setting, where students are continually adjusting to the environment and school breaks can affect eating habits [46]. Inclusion of baseline assessments will allow us to control for any baseline differences between schools. Raters will be masked to avoid potential bias. Moreover, conducting independent double ratings of ~ 20% of meals will further minimize the influence of any potential bias. Finally, this study’s internal validity is enhanced by matching schools on key variables prior to randomization, so that they differ primarily on presence of a salad bar [45]. Matching procedures were carefully developed to evaluate how school-level factors of race/ethnicity and SES might moderate the impact of salad bars. Other variables that could potentially vary between schools and impact outcomes will be carefully monitored and considered in analyses (e.g., NSLP participation or school environment factors). Plate waste assessments will be conducted in wait list control schools during two consecutive years; however, students will not know the purpose of the assessments, and their prior experience with these (minimally obtrusive) methods is not likely to alter dietary behaviors during the following school year.

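### Stratification by sex and by school category is triggered by main effects, which cannot show whether the response to salad bars differs between groups

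*Protocol article*

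**What the plan says.** All statements are in the protocol article.

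- **Sex** (Statistical analyses, Analyses): "Sex differences will be assessed for all outcomes; if significant differences are found, analyses outlined below will be stratified by sex". The analyses that follow include the one for the primary outcome, FV consumption.
- **School category** (same section, last paragraph). The purpose and the method stand in one sentence, which begins: "To examine the potential differential responses to salad bars among sociodemographic groups, main effects for Title I status and race/ethnicity school group (A through D". The consequence follows: "If main effects are observed, models will be stratified by sociodemographic group and moderator analyses considered as appropriate".
- **Moderation is a declared purpose.** The Design section says: "Matching procedures were carefully developed to evaluate how school-level factors of race/ethnicity and SES might moderate the impact of salad bars". The end of the Background and the Discussion also name the moderating role of these school-level factors.
- **Size of the strata** (Design): "16 different schools will be included (A1➔D4), 4 from each sociodemographic category", and "There will ultimately be 12 pairs of matched schools (12 Intervention" and as many Control).

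Neither rule names an interaction with arm as its trigger. The Power analysis section gives detectable effects for the unstratified comparison only.

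**The concern.** A main effect of sex or school category on intake means that the groups eat different amounts. A differential response to salad bars means that the Intervention-versus-Control difference in change varies across groups. That is an arm-by-time-by-group interaction. The two are separate quantities, and either can be present without the other.

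The written rule can therefore err in both directions:

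- If groups differ only in level, the models are split although one pooled effect would describe the data.
- If the salad bar helps one group and not another while average levels are alike, nothing prompts a moderator analysis.

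Once the models are split, readers will tend to compare significance across strata, which is not a test of moderation. The number of tests rises, and for the category split each test rests on very few schools.

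**Working it through.** **1. Reproducing the protocol's figure.** Inputs from Power analysis: J = 16 schools, n = 295 lunches per school, ICC (ρ) 0.01, 0.05 and 0.10, α = 0.05, power 80%; tests are two-sided (Analyses).

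MDES = [t(0.975, df) + t(0.80, df)] × √(4(ρ + (1−ρ)/n)/J), with df = J − 2 = 14.

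At ρ = 0.05: (2.145 + 0.868) × √(4 × 0.0532/16) = 3.013 × 0.1153 = 0.348. The three ICCs give 0.174, 0.348 and 0.484. The protocol states 0.17, 0.35 and 0.48, so its figure reproduces and serves as the yardstick.

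**2. Pairs per category.** 12 pairs / 4 categories = 3 pairs, drawn from 4 distinct schools because each year's controls become the next year's intervention schools.

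**3. The same formula within strata.**

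| Analysis set | df | ICC 0.01 | ICC 0.05 | ICC 0.10 |
|---|---|---|---|---|
| Pooled, 16 schools | 14 | 0.17 | 0.35 | 0.48 |
| One sex, 16 schools, about 147 lunches each | 14 | 0.20 | 0.36 | 0.49 |
| Title I stratum, 6 pairs as 12 clusters | 10 | 0.21 | 0.41 | 0.58 |
| One category, 3 pairs as 6 independent clusters | 4 | 0.35 | 0.70 | 0.97 |
| One category, 3 pairs, paired, no gain from matching | 2 | 0.51 | 1.01 | 1.41 |
| One category, 4 distinct schools only | 2 | 0.62 | 1.24 | 1.72 |

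For example, 6 clusters at ICC 0.05: (2.776 + 0.941) × √(4 × 0.0532/6) = 3.717 × 0.1884 = 0.70.

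A pre-post paired version, assuming half the school variance is stable, uses [t(0.975, P−1) + t(0.80, P−1)] × √(4(0.025 + 0.95/295)/P). It gives 1.04 for P = 3, 0.48 for P = 6 and 0.30 for P = 12.

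At the protocol's own detectable effects, power in one category falls from 80% to about 28–30%, 19–20% or 14–15% under the three category rows.

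**4. If collection stops after Year 2.** The Discussion reports Year 1 complete, most of Year 2 complete, and one pair without post-ratings. At most 2 pairs per category remain, and the category of the cancelled pair has one complete pair.

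**5. How easily the sex trigger fires.** Sex varies within school; equal numbers of each sex are assumed. The difference detected with 80% power is (z for α + 0.84) × √(4/N):

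- N = 14,160 lunches, uncorrected: 2.80 × √(4/14160) = 0.047 SD.
- N = 7,080 (one time point), uncorrected: 0.067 SD.
- N = 7,080, Bonferroni over an assumed 10 outcomes: 3.65 × √(4/7080) = 0.087 SD.

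**6. Whether the trigger finds what it is meant to find.** A simulation of 16 schools at ICC 0.05, uncorrected α = 0.05, 5,000 runs, with assumed effect sizes:

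| Truth | Main-effect trigger fires | Interaction test significant |
|---|---|---|
| Sex main effect 0.10 SD, no interaction | 94% | 5% |
| Arm-by-sex interaction 0.20 SD, no main effect | 5% | 94% |

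The main-effect trigger fires at its nominal 5% rate when only moderation is present.

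**The case against.** Several points on the other side stand.

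- **The sex rule does little harm to precision.** Both sexes are in every school, so the split keeps all 12 pairs. Strata of three pairs come only from the category rule.
- **A reader might infer that the primary analysis is replaced.** The text does not say so. The Analyses section specifies the Intervention-versus-Control comparison without conditions, and the category main effects are to be examined within those analyses, so a pooled model is fitted first. The sex sentence is firmer, but it does not say the overall result goes unreported. What remains is that nothing commits to reporting it whatever the tests show.
- **A reader might infer that moderation is never examined.** The category rule does allow moderator analyses. They are, however, conditional on a main effect and discretionary, so the trigger is not cured. The trigger is also a stated rule, not a detail left to a fuller document.
- **A reader might infer that Title I and category cannot both be estimated.** Title I status is fixed by category (A and B no, C and D yes), but nowhere does the protocol put both in one model. This is a caution for the fix, not an error in the plan.
- **The sex trigger need not fire.** Tests are to be corrected for multiple comparisons, and the documents give no expected sex difference. On 7,080 lunches, uncorrected, a true difference of 0.05 SD would be significant with a probability of only 56–60%.
- **The cost of a category split depends on assumptions**, so a range is the honest statement. If the sociodemographic group means Title I status, 6 pairs remain per stratum.

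**Conclusion.** The concern holds for the trigger. The protocol aims to examine differential responses but tests differences in level, and it stratifies on the result. This can split models without effect modification and miss moderation that has no main effect.

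At ICC 0.05, against the pooled 0.35 SD:

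- A category split raises the detectable effect to about 0.70 (6 independent clusters), 1.0 (paired, 2 df) or 1.24 (4 distinct schools).
- A Title I split raises it to about 0.41 to 0.48.
- A sex split leaves it at about 0.36. Its faults are the trigger and the doubled tests, and a sex difference of about 0.05 to 0.09 SD would set it off with 80% power.

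These figures rest on the protocol's cluster size and ICC, equal numbers of each sex, the assumed stable variance for the 0.48, and the assumed number of outcomes for the upper end of the sex range. The mismatch between aim and test depends on none of them. The documents do not support saying that the primary analysis is lost or that the moderation aim is abandoned.

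**What to change.** 1. Delete both main-effect triggers.
2. State that the pooled Intervention-versus-Control model, with sex, grade and school category as covariates, is the primary analysis and is always reported.
3. Test moderation directly through pre-specified secondary interactions: arm × time × sex, arm × time × Title I and, in a separate model because category determines Title I, arm × time × category.
4. Report each interaction estimate with its interval. Show stratum estimates from these models descriptively.

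The cost is analysis wording only; no data collection changes. The downside is imprecision for school-level factors. Counting 16 schools at ICC 0.05, each Title I half has 8 clusters and a standard error of 0.163. The difference between halves has 0.163 × √2 = 0.231, twice the pooled 0.115, so the detectable interaction is roughly 2 × 0.35 = 0.70 SD. The tests for school-level factors should be labelled exploratory.
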